## **The endpoints of the study**

### *Primary endpoint*

- The combined incidence of late miscarriages and preterm births. This includes spontaneous births, induced vaginal deliveries and operative deliveries on medical indications.

*Secondary endpoints*

- No. of patients treated with vaginal progesterone indicated by short cervix as a sign of imminent preterm delivery
- NICU admissions and total number of days in NICU/baby
- No. of patients hospitalized (except delivery and post partum)
- Total number of hospitalization days/ hospitalized participant
- The incidence of gestational diabetes mellitus
- The prevalence of :
  - Preeclampsia ○
  - Hypertension in pregnancy
- Vaginal bleeding in pregnancy

*Tertiary endpoints*

- Safety of treatment with metformin
- Weight gain in pregnancy
- Newborn data
- Birth weight
- Birth length
- Head circumference
- Apgar score/
- pH and base excess(BE) from umbilical cord blood

- Malformations

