### **“Drop outs”**

Data will primarily be analyzed according to the “intention to treat” principle, therefore data from patients who stop medication or do not present at pre-scheduled visits will also be included in the data analysis.

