### **Statistical analyses**

Statistical analysis of the data will be performed when all data are collected and quality checked. Data will be analyzed by an experienced statistician at Unit for Applied Clinical Research according to the “pentablind” approach.

The main outcome (late abortions and preterm births) will be the end points by intention to treat (ITT) analyses. However, secondary “per protocol” analysis will also be performed. The metformin group will be compared to the placebo group using non-paired parametric and non-paired non-parametric methods as appropriate. Only two-sided tests will be used.

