### *Risk of type I errors*

The probability of a type I error is the probability of rejecting the null hypothesis when the null hypothesis is true. This is commonly referred to as the significance level of a test. Since we consider late miscarriages and preterm delivery to be a continuum, our study has only one primary endpoint. With only one primary endpoint, and a significance level of  $p = 0.05$  and two-sided test we consider the risk of type I error extremely small and acceptable.

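### Hospital days are averaged over admitted women only, so this secondary endpoint can rise, stay flat or fall while total hospital days fall

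*Protocol*

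**What the plan says.** In the protocol's endpoint section, two bullets under *Secondary endpoints* concern maternal admission. One is a count, "No. of patients hospitalized (except delivery and post partum"). The next is "Total number of hospitalization days/ hospitalized participant". The exclusion of delivery and post partum stays is written for the count and is not repeated for the days.

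A third bullet in the same list, "NICU admissions and total number of days in NICU/baby", uses the baby as its unit and does not restrict the denominator to babies who were admitted.

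The section on drop-outs sets intention to treat as the main principle: "therefore data from patients who stop medication or do not present at pre-scheduled visits will also be included in the data analysis". The *Statistical analyses* section gives one general rule for comparison: "The metformin group will be compared to the placebo group using non-paired parametric and non-paired non-parametric methods as appropriate". Nowhere does the protocol define hospital days over all randomised women, assign zero days to women never admitted, or say that the two hospitalisation bullets are to be read together.

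**The concern.** Admission happens after randomisation, and the protocol lists it as an outcome. Its adverse-event section also names preeclampsia, preterm delivery, bleeding and other study endpoints as conditions that may lead to hospitalisation, so an effect of treatment on admission is plausible. If there is one, the women admitted on metformin and those admitted on placebo have passed through different filters. Randomisation does not protect a comparison between them.

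At stake is the reading of one secondary endpoint. A difference in mean stay among admitted women could be reported as harm, benefit or no effect when total hospital use in the randomised arms says something else. An analysis plan could choose the test, but it could not bring never-admitted women into the comparison without changing the endpoint that the protocol has written.

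**Working it through.** **Inputs.** From the protocol: 500 women per arm (*Power calculation*) and equal allocation (*Randomization*, blocks of five and five). The protocol gives no admission rate, length of stay or standard deviation. Every admission figure below is therefore an assumption chosen for illustration.

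**The protocol's own figure.** The only one involved is the arm size, which serves here as a divisor. For 10% against 5%, two-sided 0.05 and 85% power, with pooled variance under the null:

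n = [1.960 × √(2 × 0.075 × 0.925) + 1.036 × √(0.10 × 0.90 + 0.05 × 0.95)]² / 0.05² ≈ 497 per arm.

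Power with 500 per arm is 85.2%, so the stated 500 reproduces.

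**General rule.** Let the placebo arm have H admitted women and T days in total. Suppose treatment prevents h of those admissions, which would have used d days, and leaves the other stays unchanged. The endpoint moves from T/H to (T − d)/(H − h). This is a rise exactly when H(T − d) > T(H − h), which simplifies to d/h < T/H. So:
- prevented stays shorter than average: the endpoint rises;
- prevented stays equal to the average: it does not move;
- prevented stays longer than average: it falls.

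In all three cases total days fall by d, and days per randomised woman fall by d/500.

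**Illustration.** Assume 100 stays of 2 days and 50 stays of 10 days among 500 placebo women.

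| Assumed effect of treatment | Women admitted | Total days | Days per admitted woman | Days per randomised woman |
|---|---|---|---|---|
| None (placebo) | 150 | 100×2 + 50×10 = 700 | 4.67 | 1.40 |
| Half the short stays prevented | 100 | 50×2 + 50×10 = 600 | 6.00 | 1.20 |
| Half the short and 20% of the long prevented | 90 | 50×2 + 40×10 = 500 | 5.56 | 1.00 |
| Half of both prevented | 75 | 50×2 + 25×10 = 350 | 4.67 | 0.70 |
| Half the long stays prevented | 125 | 100×2 + 25×10 = 450 | 3.60 | 0.90 |

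In the second row the protocol's endpoint looks 29% worse (6.00/4.67) while days per randomised woman are 14% lower (1.20/1.40). In the fourth row total days halve and the endpoint does not register it. In the last row the direction is right, but the ratio falls 23% against 36% per randomised woman.

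**Range.** Short and long stays of 2 and 10, 2 and 5, or 3 and 14 days were combined with 50, 100 or 150 short and 25 or 50 long stays, giving 18 settings. With half the short stays prevented, the endpoint rises in all 18. The smallest rise is 13% (425/175 = 2.43 to 275/100 = 2.75) and the largest is 30% (800/200 = 4.00 to 650/125 = 5.20). Days per randomised woman fall in all 18, by between 8% (1.20 to 1.10) and 35% (0.85 to 0.55).

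**The case against.** The best defence is that the two maternal bullets work as a pair. The number admitted is counted over the whole arm, and admitted women times mean stay gives total days. In the second row of the table a reader would see 150 v 100 admitted beside 4.67 v 6.00 days and could recover 700 v 600. This stands as a partial offset. It does not turn the comparison of days into a randomised one, and the protocol does not require joint reading.

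It can also be said that no test is named for this endpoint. The comparison rule is general, with methods to be chosen as appropriate, and an analysis plan that is not shown may treat the ratio as description. That is fair as to the test. The denominator, however, is fixed in the protocol.

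Three stronger readings are tempting and are not supported:
- A reader might infer that metformin is intended to change admissions. The *Hypothesis* section speaks only of late miscarriage and preterm birth; admission is simply a listed outcome.
- A reader might infer that the admitted women in the two arms are certain to differ. If treatment does not affect admission, they remain comparable.
- A reader might infer that the endpoint will point the wrong way. That needs the prevented stays to be shorter than average, and nothing in the protocol shows which pattern to expect.

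Finally, this is one of several secondary endpoints. The sample size and the type I error statement rest on the single primary endpoint.

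**Conclusion.** The point holds in a limited form. As defined, the endpoint conditions on a post-randomisation event that treatment may affect, which sits badly with the protocol's intention-to-treat principle. Its direction need not follow that of total hospital use. The rule for when it rises is exact arithmetic, given that the stays not prevented are unchanged. The sizes shown (a rise of 13% to 30% while days per randomised woman fall by 8% to 35%) rest wholly on assumed admissions and one assumed pattern of effect. They show what can happen and are not a forecast for this trial. The primary analysis and its power are not touched. The definition should be changed because the change is small and the present wording cannot be repaired by the choice of test.

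**What to change.** In the secondary endpoint list:
- Replace the days bullet with hospital days per randomised woman, counting 0 for women never admitted, compared in all randomised women by allocated arm.
- State whether the exclusion of delivery and post partum stays applies to the days as it does to the count.
- Keep days per admitted woman as description beside the number admitted, without a p-value.

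The cost is a few words in the endpoint list. No new data are needed, since the two existing bullets already require admission status and days.

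There are two small downsides. The new variable is skewed with many zeros, so the method must suit that, for example a mean difference with a bootstrap interval or a rank test. Antenatal days also depend on how long the pregnancy lasts: a drug that prevents late miscarriage and preterm birth gives women more time in which to be admitted. Gestational length should therefore be reported alongside. The comparison stays a randomised one, but a reader needs that context to interpret it.

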## **Methods**

### *Design*

Prospective, randomized, double-blind, Nordic multi-centre study

### *Participating centres*

Public or private, secondary or tertiary clinics dealing with gynaecology and obstetrics. We will invite centres from the Nordic countries. All principal investigators in all study centres have to be specialists in obstetrics/gynecology or under on-going specialist-training.

### *Inclusion criteria*

- Age: 18-45 years
- PCOS diagnosed according to Rotterdam 2003 criteria,
- Mode of conception: Any
- Single, viable fetus, diagnosed by vaginal ultrasound
- Gestational week at inclusion: week 6 + 0 to 12 + 6.
- Wash out for metformin: at least 7 days
- Able to communicate fluently in the official language at the study site or English

- Informed consent

### *Exclusion criteria*

- Gestational age > 12 weeks+6days
- Any type of diabetes (except GDM in former pregnancy).
- Known liver disease or ALAT > 100 IU/L
- Known renal disease, renal dysfunction or serum creatinine > 110 µmol/L .
- Acute conditions that may worsen renal function, such as dehydration, septicaemia, cardiovascular collapse (shock), and intravascular administration of iodinated contrast.
- Acute or chronic conditions that can lead to tissue hypoxia, such as cardiac or respiratory failure, recent myocardial infarction or shock.
- Known hypersensitivity to any component of metformin
- Breastfeeding
- Known alcohol or drug abuse
- Use of drugs interfering with metformin: erythromycin (or other macrolides), cimetidin, anticoagulation therapy
- Unsuitable for participation of any other reasons

### *Study medication*

- Metformin 500 mg x 2 daily the first week and then 1000 mg x 2 daily from the second week to delivery.

Protocol for The PregMet 2 Study; version 7  
2013-11-25

- Placebo 1 tablet x 2 daily the first week. And then 2 tablets x 2 daily from the second week to delivery.
- To counteract a possible metformin action on folic acid and vitamin B12 levels, patients will be advised to take the daily dose of folic acid recommended in the country of the study centre. Further, one daily multivitamin tablet containing vitamin B6 and B12 will be recommended.
- Both metformin and placebo are produced by Weifa A/S. The tablets will be packed into boxes at the Hospital Pharmacy in Trondheim. After randomization the medication will be sent to cooperating pharmacies at the study site.
- The Hospital Pharmacy in Trondheim is responsible for medical accounting in the trial.
- A separate drugaccountability log will be registered at each site.

*Patients included in the PregMet 2 Study*

- The overall intention and philosophy of the trial, is that included patients should receive the recommended and appropriate treatment available at each country and centre.
- Participation in the study does not limit any kind of diagnostic evaluation, examination or treatment option regarded as necessary during pregnancy.
- The participants in the PregMet 2 study can however not participate in other medical trials during the actual pregnancy.

- Patients can only be included in the PregMet 2 Study once.

*Progesterone treatment to prevent preterm delivery*

In Iceland vaginal progesterone administration is used to prevent preterm delivery according to national guidelines;

1. In multiparous women who had former preterm delivery and
2. In women where cervix is found to be < 15 mm before gestational week 32. There are however no screening program for cervix length for asymptomatic women.

These treatment regimens interfere with the primary endpoint of the PregMet study. Therefore to avoid protocol violation and ethical conflict we decide the following:

1. At study centres in countries where progesterone is used prophylactic in multiparous women with former preterm birth, only nulliparous women will be included in the study.
2. In women with signs or symptoms of imminent preterm delivery, the routine treatment at the study centre should be given, - included vaginal progesterone treatment.
3. Vaginal progesterone treatment in such cases of imminent preterm delivery will be registered as a secondary endpoint.

If the progesterone treatment routine is introduced in other participating countries during the on-going study, these countries will adhere to the instructions above.

*Pre-inclusion evaluation - screening*

- Information (verbal and written to the potential participating woman).
- Signed written informed consent.
- Confirming the diagnosis of PCOS; anamnestically and from patient records

□

Vaginal ultrasound examination to verify intrauterine viable singleton fetus (visualised heart beats), gestational age  $< 12+6$  weeks. (CRL  $< 65$  mm or BPD  $< 23$  mm)

- Blood tests:
- fasting plasma or serum glucose,
- serum ALAT
- serum creatinine

Standardized interviewer-administered CRF will be used to obtain self-reported data on former medical and gynecologic/obstetric history, ethnicity, and employment, smoking habits, study medication and concomitant medication. Biometric variables, including height (measured only at inclusion), weight, blood pressure, and heart rate, are recorded at inclusion and at each pre-scheduled visits at gestational week 19, 28, 32 and 36.

*1st pre-scheduled visit:*

Inclusion gestational age  $\leq 12^{+6}$  weeks

- Written general diet and lifestyle information recommended to pregnant women from the national health authorities in each country will be given.
- Anamnestic data
- Physical examination
- Blood pressure

Protocol for The PregMet 2 Study; version 7  
2013-11-25

□

- Weight and height  
Breast-size estimation
- Hirsutism score (<http://www.hirsutism.com/hirsutism-biology/ferriman-gallweyscore.shtml>)
- Vaginal ultrasound examination:
- Visualized heart activity
- CRL and /or BPD measured
- Description of the ovaries
- Fasting blood samples (both serum and full blood) for freezing
- 2 hour OGTT (Fasting and 2h serum glucose to be measured locally)
- Questionnaire on depression EPDS (standard questionnaire used in and after pregnancy in routine pregnancy follow-up)

*2nd pre-scheduled visit:*

Gestational age 19 ± 1 week

- Anamnestic data
- Physical examination
- Blood pressure
- Weight
- Ultrasound examination:
- Mid-pregnancy determination of term

□

Doppler measurement of the uterine artery (OPTIONAL)

- Fasting blood sample (both serum and full blood) for freezing
- Fasting blood sample for glucose

*3rd pre-scheduled visit:*

Gestational age  $28 \pm 1$  weeks

- Anamnestic data
- Physical examination
- Blood pressure
- Weight
- Ultrasound examination (Doppler) OPTIONAL
- 2 hour OGTT (Fasting and 2h serum glucose to be measured locally)
- Blood samples (both serum and full blood) for freezing
- Questionnaire on depression EPDS (standard questionnaire used in and after pregnancy in routine pregnancy follow-up)

*4th pre-scheduled visit:*

Gestational age  $32 \pm 1$  weeks

- Anamnestic data
- Physical examination ○ Blood pressure

Protocol for The PregMet 2 Study; version 7  
2013-11-25

- Weight
  - Ultrasound examination:
    - Fetometry
  - Fasting blood samples (both serum and full blood) for freezing
  - Fasting blood sample for glucose
- 

*5th pre-scheduled visit:*

Gestational age  $36 \pm 1$  weeks

- Anamnestic data
  - Physical examination ○ Blood pressure ○ Weight
    - Breast-size estimation
  - Fasting blood samples (both serum and full blood) for freezer
  - Fasting blood sample for glucose
- 

*At delivery*

- Collecting maternal data from the delivery and clinical data from the newborn
- Sampling of arterial and venous cord blood immediately after birth (OPTIONAL)
- Sampling of placenta biopsies (OPTIONAL)

*At 8-weeks postpartum: Structured telephone interview on*

- Birth experiences
- Breastfeeding experiences
- Questionnaires on postpartum depression
- Complications postpartum: infections, deep venous thrombosis, lung embolism, mastitis, other serious adverse events
- New born hospitalization, illness, anomalies
- Left over study medication reported
- Questionnaire on depression EPDS (standard questionnaire used in and after pregnancy in routine pregnancy follow-up)

*Blood samples*

All blood samples will be collected in the morning between 08 and 11, and after an overnight fast. All screening analyses will be analysed at the local hospital.

Ten (10) test tubes of whole blood from each patient are centrifuged after 20 minutes, and serum is filled in nine (9) cryotubes with at least 1.8 ml of serum in each, and frozen at – 70 ° C (or – 80 ° C if that is preferred). Four EDTA tubes with whole blood will be filled, turned up and down a couple of times and transferred into cryotubes and freezed.

Two tubes for “buffy coat” will be separately centrifuged, processed and freezed.

All cryotubes will be marked with a unique barcode. The tubes will be marked with a colour code for each visit. (Red hat for inclusion, yellow in week 19, blue in week 28, green in week 32, brown in week 36.

Umbilical cord blood will be sampled at delivery (optional). We aim to have both venous whole blood samples, and both arterial and venous serum samples (Handled as described above). These will be marked with a purple hat.

All serum and whole blood will be sent to: [name]/ or study midwife, Fødeavdelingen, Kvinneklivikken, St. Olavs Hospital, [name], Norway ( [contact] E-mail [contact]). Ahead of shipment the receiver should be contacted. No shipment is to be done on Thursdays, Fridays or the last two days before a public holidays.

### **Study duration**

For each woman the participation in the present study will last from inclusion till 8 weeks post partum. The study medication will be stopped at delivery, but data will be collected and adverse events reported until the 8th week post partum.

### **“Drop outs”**

Data will primarily be analyzed according to the “intention to treat” principle, therefore data from patients who stop medication or do not present at pre-scheduled visits will also be included in the data analysis.

## Clarification:

«**Drop-out**»: is a general term for those patients included in a study who

- Clearly state that they do not want to continue in the study, (-they will not meet at pre-scheduled visits in the study) OR
- Clearly state that they do not intend to take any more study medication OR
- Clearly state that they do not want any contact with the study investigators

**NOT “Drop-out”**: patients who

- Miss/forget an appointment, but attend other visits
- Reduce or do not take study medication because of side effects □ Forget to take their study medication, but intend to take it.

**In our “intention-to-treat analyses” we will include data from all “drop-outs”. This is the meaning of “intention-to-treat”.**

Data included from drop-outs are:

- already collected data and samples and
- Information from delivery mother/baby. (The informed consent has not been withdrawn)
- **Already collected data will not be destroyed or deleted routinely**, but if the patient explicitly asks for it (withdraws informed consent); we will delete it and not collect information from her delivery and baby at delivery.

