## Withdrawal from the study

Patients may withdraw from the trial at any time. If a patient withdraws from the trial she will be asked if the material already collected and information about the future delivery can be collected and included in the trial data base. If the patient requests, all information about the patient will be withdrawn. This is described in the informed consent. We wish to include and follow 1000 women in our trial. In our former studies withdrawal was a very minor problem, thus we expect a similar pattern in this trial, indicating no substitute is necessary. If this

proves to be a problem in accordance to keep our desired sample size, we might open up to include additional patients as long as the inclusion period is not stopped.

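### Declaring a stop of study drug is enough to make a woman a drop-out, and the data listed for drop-outs omit the later visits and the 8-week contact

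*Protocol*

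**What the plan says.** The Clarification under Drop outs gives three triggers for drop-out status, joined by OR: declaring a wish not to continue in the study, declaring no further use of study drug ("Clearly state that they do not intend to take any more study medication OR"), and declaring a wish for no contact. Only the first carries the remark that the woman will not come to scheduled visits.

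A second list names women who are not drop-outs. It includes those who "Reduce or do not take study medication because of side effects". That entry is not limited to temporary stops; the intention to resume is attached only to the entry on forgetting tablets.

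One data list then applies to all drop-outs: "already collected data and samples and" information on mother and baby from the delivery, provided consent has not been withdrawn.

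The surrounding text is broader:

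- Study duration: "For each woman the participation in the present study will last from inclusion till 8 weeks post partum", with data and adverse events collected to the end of that period.
- The paragraph opening Drop outs: "data from patients who stop medication or do not present at pre-scheduled visits will also be included in the data analysis".
- Withdrawal from the study: a woman who leaves the trial is asked whether "the material already collected and information about the future delivery can be collected and included in the trial data base".

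**The concern.** Stopping a drug and leaving follow-up are different events, and an intention-to-treat analysis depends on keeping them apart. The Clarification puts both under one label and gives that label one data list. That list has about the same scope as what is sought from a woman who withdraws from the trial. A site that applied it literally could stop collecting visit data once a woman said she would take no more tablets.

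Visit-based secondary and tertiary outcomes are exposed. "The incidence of gestational diabetes mellitus" is a secondary endpoint. Its main measurement is "2 hour OGTT (Fasting and 2h serum glucose to be measured locally"), scheduled at inclusion and again only at week 28. If the week 28 test is not done, no later analysis can recover it. Blood pressure, weight gain and post partum adverse events depend on the same visits or on the 8-week interview. The count of remaining tablets under Adherence is also taken at that interview.

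The overlap between the two lists adds inconsistency: two sites could classify the same side-effect stop differently.

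**Working it through.** **Reading the rules together.** Take a woman who declares at week 20, because of nausea, that she will take no more tablets but is willing to attend visits.

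1. Drop-out triggers: she meets the second. Because of the OR, that is sufficient.
2. Not-drop-out list: she also meets the side-effects entry. Side effects foresees stopping the drug for this reason, so the case is expected. No precedence is stated.
3. If she is classed as a drop-out, the data list covers what was collected up to week 20 plus delivery information. The visits at weeks 28, 32 and 36 and the 8-week interview are not named.
4. Study duration has her participating, with data and adverse events collected, to 8 weeks post partum. This is the explicit contrast.
5. The opening paragraph of Drop outs includes her data with no time window. It is broader than the list but does not say that post-stop visits must take place, so it is not a clear contradiction.

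**Size.** The protocol states no figure on this point and no rate of declared stops. Withdrawal from the study says only that withdrawal was a very minor problem earlier. Illustrative ceilings can be taken from PregMet 1, assuming it carries over to 500 per arm. (That planned size reproduces: 10% against 5%, 85% power, two-sided 0.05, pooled variance without continuity correction gives 497 per arm.)

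*GDM rate.* Table 1: (22 + 21)/(125 + 124) = 43/249 = 17.27%.

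*Ceiling A, from compliance.* The good-compliance rule under Pooled data and per protocol analyses allows no tablets for at most 2 weeks. A woman who stops for good before week 28 and stays pregnant more than 2 further weeks therefore fails it. Non-compliance was 100% − 84% = 16% as stated, or 1 − 108/135 = 20% from the denominators. That gives 0.16 × 500 = 80 to 0.20 × 500 = 100 per arm. It also counts dose reducers, late stoppers and side-effect stoppers.

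*Ceiling B, from the GDM denominators.* (135 − 125)/135 = 7.4% on metformin and (135 − 124)/135 = 8.1% on placebo are outside the new-GDM denominator, reason not given. That is 37 and 41 per 500.

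*Precision of the GDM difference.* Half-width = 1.96 × √(2 × 0.1727 × 0.8273 / m), with m women tested per arm:

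| m per arm | Basis | Half-width (percentage points) |
|---|---|---|
| 500 | all tested | 4.69 |
| 463 | ceiling B, metformin rate | 4.87 |
| 459 | ceiling B, placebo rate | 4.89 |
| 420 | ceiling A, 16% | 5.11 |
| 400 | ceiling A, 20% | 5.24 |

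**The case against.** The strongest reply is that nothing in the protocol ends visits for women who stop the drug. Only the first trigger mentions not attending. The visit schedule has no exception for women off drug, and Study duration covers every woman. The data list follows a sentence promising to include data from all drop-outs, so it can be read as a minimum. Data from a visit attended after the stop would also be already collected by the time of analysis. **This stands** as far as it goes: a careful site could follow the general rule, and a reader who inferred that the protocol orders visits to stop would be going beyond the text. It does not remove the problem, because the Clarification is where a site would look to learn what drop-out status means, and it omits those visits.

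Second, the side-effects entry is the more specific rule and may be meant to prevail. That is sensible, and it would shrink the affected group to women who stop for other reasons. But the protocol does not say so.

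Third, ceiling A may be too high. In PregMet 1 about 22 to 27 women per arm were non-compliant (16% to 20% of 135), yet at most 10 or 11 lacked a GDM result, so roughly half or more of the non-compliers had one. **This is fair**, provided that PregMet 1's follow-up practice carries over as well as its compliance. The protocol does not describe that practice, so ceiling B is not a firm bound on what a literal reading would lose.

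Fourth, the lost tablet count matters little, since intake is asked about at every visit and is nil after a declared stop. That also stands.

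**Conclusion.** The point holds as a drafting fault that creates an avoidable risk to secondary and safety data. It rests on the OR in the drop-out definition, on a data list that leaves out post-stop visits and the 8-week contact, and on the unresolved overlap for side-effect stops.

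Its size cannot be derived. Under the illustrative PregMet 1 ceilings, the GDM half-width grows by about 0.2 percentage points (ceiling B) or 0.4 to 0.6 points (ceiling A), a small to modest loss. Both ceilings overstate the declared stops themselves, since they count women for other or unknown reasons. GDM found in routine care might still be recorded.

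Three stronger conclusions are tempting but unsupported:

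- *The primary endpoint is compromised.* Delivery information is kept and drop-outs stay in the intention-to-treat analysis. The list does not name late miscarriage, but nothing excludes it.
- *The comparison is biased.* More side-effect stops on metformin could make losses differ by arm, but the protocol gives no stop rates by arm, and the Table 1 gaps (10 and 11 of 135) are nearly equal.
- *The Clarification flatly contradicts the intention-to-treat paragraph.* That paragraph sets no time window; the firm contrast is with Study duration.

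**What to change.** Delete the trigger on taking no more study drug from the drop-out definition. Add a sentence that stopping or reducing study drug, for any reason, does not end participation. Scheduled visits, the week 28 glucose tolerance test, delivery or late-miscarriage data and the 8-week interview then continue and enter the intention-to-treat analysis, unless the woman declines visits or withdraws consent. This also removes the overlap with the side-effects entry.

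The cost is a wording change. It adds no visit or test beyond the existing schedule and does not alter the sample size. Some women who stop the drug will still decline visits, so some data will remain missing.
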